## Abstract

Obesity is a growing health and economic burden. This study investigates dexamphetamine, an inexpensive drug, as a potential safe and effective treatment for obesity when combined with diet and lifestyle changes over six months in general practice. The trial is a double-blind, randomised, placebo-controlled study with a six-month active treatment phase and two years of follow-up. Participants are randomised 1:1 to receive either dexamphetamine or placebo, starting at 5 mg twice daily, with weekly titration up to 30 mg twice daily as tolerated. Weekly reviews during titration assess tolerability and support lifestyle modifications, followed by monthly reviews during the maintenance phase. Dose adjustments are guided by clinical effects and a standardised amphetamine rating scale, with gradual down-titration during the final month. If demonstrated to be effective and safe long-term, dexamphetamine could provide a scalable, practical solution to reduce the individual and societal burden of obesity.

## Specifications table

**Table utbl0001:** 

**Subject area**	Medicine and Dentistry
**More specific subject area**	Obesity management
**Name of your protocol**	A double-blind randomised controlled trial protocol comparing dexamphetamine and placebo effectiveness for obesity management in primary care settings
**Reagents/tools**	Aspen Dexamphetamine sulfate 5 mg tablet
**Experimental design**	This is a double-blind randomised placebo-controlled trial of a 6 month active treatment period followed by 2 years of observation. Participants are randomised 1:1 to either immediate release dexamphetamine 5 mg tablets or placebo tablets. The dose starts at 1 tablet twice daily and is up titrated weekly by 1 tablet twice daily as tolerated, to a maximum of 6 tablets (30 mg) twice daily. Participants are reviewed weekly during titration to assess medication tolerability and to reinforce positive lifestyle behaviours, followed by monthly reviews at maintenance dose. Dosage adjustment is guided by clinical effects, and a standardised rating scale for amphetamine effects. The dose is down titrated over the last month of the treatment period and then ceased.
**Trial registration**	Australian and New Zealand Clinical Trials Registry (ANZCTR) ACTRN12625000764437p
**Ethics**	This study involves human participants, and informed consent will be obtained from all participants prior to their inclusion in the study, in accordance with ethical standards.
**Value of the Protocol**	• This research will provide valuable insights into how DEX can be integrated into current obesity management protocols
	• Assess the implementation, safety and feasibility of using DEX to treat obesity in general practice settings
	• DEX offers a promising alternative that balances efficacy, affordability, and accessibility

## Background

This study investigates the potential of dexamphetamine (DEX) as a novel, cost-effective treatment for obesity, using individualised dose titration over a 6-month period. Drawing on extensive clinical experience with DEX in the treatment of attention deficit hyperactivity disorder (ADHD), this trial aims to repurpose a well-established and relatively safe medication to support weight loss, alongside sustainable dietary and lifestyle modifications [1]. If successful, the study may define a therapeutic dose range for obesity and demonstrate that DEX, when combined with behavioural support, can achieve clinically meaningful outcomes.

Compared to other Therapeutic Goods Australia (TGA) approved anti-obesity pharmacotherapies, which are often prohibitively expensive, DEX represents a more affordable alternative. This is particularly relevant for individuals from socioeconomically disadvantaged backgrounds, who experience higher rates of obesity and have limited access to treatment options [2]. Broadening access to effective pharmacotherapy could, therefore, have a substantial positive impact on public health. However, proper titration protocols and safety measures must be firmly established before wider clinical use.

For implementation in general practice, several key components are required. First, general practitioners (GPs) must receive comprehensive education on DEX titration principles, patient monitoring, and safety protocols. Clinical guidelines will be essential to assist GPs in identifying appropriate patients, including those with minimal cardiovascular or psychiatric risk factors. Integration of care through collaboration between GPs, dieticians, and mental health professionals will ensure a holistic approach that addresses both the pharmacological and behavioural aspects of obesity management.

Safety remains a primary consideration. Although DEX is approved for long-term use in children as young as six with ADHD and increasingly prescribed to adults in the form of lisdexamfetamine, prescribing regulations vary across Australian states [3]. In some regions, GPs are authorised to prescribe stimulants, while others impose restrictions. Advocacy for uniform national policies would help ensure equitable access and consistent standards of care.

The outcomes of this study could pave the way for larger trials evaluating DEX as a time-limited intervention for adults with overweight or obesity. If long-term efficacy and safety are demonstrated, DEX could represent a scalable, practical solution that reduces the burden of obesity both at the individual and societal levels. Ultimately, integrating DEX into routine care could expand the treatment toolkit available to GPs and improve outcomes for a population in critical need of effective intervention.

## Description of protocol

### Study aim

The primary aim of this study is to evaluate the implementation, safety, and feasibility of DEX as a treatment for obesity in general practice settings. The study will assess how DEX can be incorporated into routine primary care and its potential role as an accessible and affordable therapeutic option for obesity management.

### Study objectives

#### Primary objective

To evaluate the effect of DEX treatment on body weight in patients with obesity managed in general practice.

Secondary Objectives1.To assess the cardiovascular safety of DEX treatment through monitoring of cardiovascular parameters and the occurrence of adverse cardiovascular events.2.To identify possible undiagnosed active depressive disorders at baseline prior to initiation of treatment.3.To evaluate changes in mood, cognition, and physiological responses during treatment using the Amphetamine Interview Rating Scale (AIRS).4.To assess the feasibility of implementing DEX therapy for obesity management within routine general practice care, as measured by recruitment, retention, adherence, and tolerability.

### Design overview

This study is a randomised, double-blind, two-group clinical trial conducted in a general practice setting. Eligible participants will undergo a screening and baseline assessment before being randomised in a 1:1 ratio to receive either the active medication (DEX) or a placebo, with both groups receiving identical tablets. All participants will receive exercise and dietary advice from a dietician at baseline and again at the end of the 6-month treatment phase.

During the initial 6-week dosage titration period, participants will be reviewed weekly by a clinician, followed by monthly reviews for the remainder of the 6-month treatment period and down titration. Medication will be supplied monthly to each participant. Upon completing the treatment period, participants will be reviewed one week after discontinuing their assigned study medication, with follow-up visits scheduled at one, three, and six months, and continuing every six months for a total of two years (Fig. 1).

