### Outcome measures

Outcome measures will be collected at baseline, during each dose adjustment visit, during the maintenance phase of treatment, and following cessation of medication at 1 week, and at 1, 3, 6, 12, 18, and 24 months, as illustrated in Fig. 1.

Primary Outcome• Change in Body Weight: Change in body weight from baseline measured at 6 months during treatment and at 2 years following discontinuation of study medication.

Secondary Outcomes1.Cardiovascular Outcomes: Changes in cardiovascular parameters and the incidence of adverse cardiovascular events.2.Baseline Mental Health Assessment: Identification of possible undiagnosed active depressive disorders at baseline.3.Neuropsychiatric Effects: Changes in mood, cognition, and physiological responses during treatment as measured by the Amphetamine Interview Rating Scale (AIRS).4.Feasibility will be assessed by recruitment and retention rates, treatment adherence, ability to achieve target dosing, and the frequency of adverse events or treatment discontinuation.

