### Data analysis

The primary analysis will adopt an intention-to-treat approach to ensure that all randomised participants are included in the evaluation, regardless of adherence to the treatment protocol. The primary outcome, the change in weight from baseline to both 6 months and 2 years, will be assessed using simple and multiple linear regression, adjusting for prespecified covariates such as age, sex, baseline BMI, and comorbidities. Secondary outcomes, including cardiovascular parameters, mood and cognition (AIRS scores), and feasibility metrics, will be analysed using appropriate regression models or repeated-measures mixed-effects models for longitudinal data. Missing data will be addressed primarily using available data under intention to treat; where missingness exceeds 10–15%, multiple imputation and complete-case analyses will be conducted as sensitivity analyses. Exploratory subgroup analyses by sex, baseline BMI, or baseline depressive status may also be performed. Adverse events will be summarised descriptively by type, severity, and relationship to treatment, with serious events reported individually.

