### Indications for early withdrawal

Participants may withdraw or be withdrawn from the study prematurely under specific circumstances to ensure their safety and the integrity of the research. The following criteria will guide decisions regarding early withdrawal:a)Significant Adverse Event (SAE): If a participant experiences a SAE that is deemed related to the intervention, they will be promptly withdrawn from the study. SAEs may include, but are not limited to, severe cardiovascular issues, psychiatric disturbances, or any other health complications that arise during the treatment period. The safety of participants is paramount, and frequent monitoring will be conducted to identify and address any adverse effects promptly. Recognised medication side effects, such as dry mouth, insomnia or mood changes will be discussed with the participant and managed according to participant toleration. Management may include a dose reduction.b)Withdrawal of Consent: If a participant chooses to withdraw, their decision will be respected. The participant will be invited to give the reason for withdrawal.

Through these early withdrawal criteria, we aim to uphold participant safety and maintain the quality and reliability of the study data. Any participant withdrawn from the study will be offered appropriate follow-up care and support as needed.

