### Optimising attendance and handling missing data

To minimise missed follow-up assessments, all participants will be contacted ahead of their scheduled visits to confirm their attendance. If necessary, assessments can be postponed or rescheduled, with appropriate documentation maintained. Attendance at assessments during the dose titration phase is mandatory before considering any dose increases. Additionally, we will strive to collect follow-up data from participants who are unable to attend appointments during the maintenance dose phase or after treatment cessation by telephone. Participants will be asked to provide measurements taken from personal weight and blood pressure measuring equipment.

While we are committed to optimising adherence, some missing data are anticipated. To address this, we will compare baseline characteristics between participants with and without assessments at 6 and 24 months to identify potential biases in our final analysis. We will also investigate the reasons for study dropouts to better understand the mechanisms behind missing data, including any adherence issues related to the study protocol. Data will be reviewed regularly to identify missing or inconsistent entries, and where possible, clarification will be sought from the treating clinician or study records.

For the primary analysis, available data will be analysed using appropriate statistical methods depending on the extent and pattern of missingness. If the proportion of missing data is low, analyses will be conducted using complete case analysis. If missing data are substantial, appropriate statistical techniques such as multiple imputation will be considered to reduce potential bias.

Sensitivity analyses may be conducted to assess the impact of missing data on the primary outcome.

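### Post-treatment visits are counted from the last tablet, so a participant who stops early but stays in the study is assured no weight at 6 months from randomisation

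*Protocol article*

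**What the plan says.** All references are to the protocol article.

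- **Design overview** sets weekly reviews during the 6-week titration, "followed by monthly reviews for the remainder of the 6-month treatment period and down titration". Follow-up comes next: "Upon completing the treatment period, participants will be reviewed one week after discontinuing their assigned study medication", then further visits out to two years.
- **Outcome measures** times these visits as "following cessation of medication at 1 week, and at 1, 3, 6, 12, 18, and 24 months". Data collection repeats that timing. Neither section repeats the condition that treatment was completed.
- **Table 1** (under Baseline measures) is laid out by treatment state: baseline, before a dose change, maintenance, and after ceasing. It has no column for time since randomisation.
- **Outcome measures** defines the primary outcome as "Change in body weight from baseline measured at 6 months during treatment and at 2 years following discontinuation of study medication".
- **Data analysis** states the population: "all randomised participants are included in the evaluation, regardless of adherence to the treatment protocol".
- **Indications for early withdrawal** takes one group out of the study, and not only off the tablets: "If a participant experiences a SAE that is deemed related to the intervention, they will be promptly withdrawn from the study".
- **Optimising attendance and handling missing data** offers to seek data from those "unable to attend appointments during the maintenance dose phase or after treatment cessation by telephone", using home equipment. It also plans to "compare baseline characteristics between participants with and without assessments at 6 and 24 months".

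**The concern.** An intention-to-treat contrast at 6 months needs a weight from every willing participant at the same time since randomisation, whether or not that person still takes tablets. The article ties its calendar to treatment state instead. It also words the 6-month outcome as an on-treatment measurement, which is undefined for someone who has stopped.

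The protocol expects such people, since treatment discontinuation is listed among its feasibility measures. If they stop because they tolerate the tablets poorly, and this happens more often on dexamphetamine than on placebo, the missing month-6 weights are neither random nor balanced between arms. The analysis would drift towards a comparison of those who stayed on treatment. A weight that was never scheduled cannot be recovered later. This is separate from the imputation rule and from the withdrawal rule, because it affects people who are still willing to attend.

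**Working it through.** **Inputs.** Post-cessation visits at 1 week and at 1, 3, 6, 12, 18 and 24 months (Outcome measures). Treatment period of 6 months (Design overview). Conversion: 1 month = 4.345 weeks. I assume that tablets start at randomisation.

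**Target.** Month 6 from randomisation = 6 × 4.345 = week 26.1.

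**Example: tablets stopped at week 6, participant stays in the study.**

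- Literal reading of Design overview: treatment was not completed, so post-treatment visits never start.
- Cessation-clock reading (Outcome measures, Data collection): visit week = 6 + offset.
  - 1 week: 6 + 1 = week 7
  - 1 month: 6 + 4.3 = week 10.3
  - 3 months: 6 + 13.0 = week 19.0
  - 6 months: 6 + 26.1 = week 32.1
- The visits nearest to week 26.1 are 26.1 − 19.0 = 7.1 weeks early and 32.1 − 26.1 = 6.0 weeks late.

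**Other stopping times, counting cessation-clock visits only (months from randomisation).**

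| Stop | Nearest visit to month 6 | Gap |
|---|---|---|
| 1 | 7 | +1 |
| 1.5 | 4.5 | −1.5 |
| 2 | 5 | −1 |
| 3 | 6 | 0 |
| 4 | 5 | −1 |
| 4.5 | 5.5 | −0.5 |
| 5 | 6 | 0 |

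On this clock a visit falls at month 6 only by coincidence, namely after a stop at about month 3, at about month 5, or one week before month 6.

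**The 2-year weight.** 24 × 4.345 = 104.3 weeks after the last tablet.

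- Stop at week 6: 6 + 104.3 = about week 110.
- Completer: 26.1 + 104.3 = about week 130.

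The same labelled time point therefore differs by about 20 weeks in time since randomisation.

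**Set against the analysis.** The calendar, Table 1 and the outcome definition all follow tablet use, while the analysis population is defined without regard to it. No section describes a participant who stops tablets and remains in follow-up, and none fixes a month-6 weight for that person.

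**The case against.** The strongest reply is that the 6-month treatment period is a calendar phase. Design overview gives the monthly reviews to participants generally and does not end them when tablets end. It also gives all participants dietary advice at the end of the treatment phase. Optimising attendance and handling missing data offers telephone weights after cessation and speaks of 6- and 24-month assessments, so month 6 is a planned assessment point. Fig. 1 is not visible here, and a procedure manual may say more.

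Much of this stands. A reader might infer that an early stopper has no visit at 6 months. The documents do not support that, because nothing says the monthly reviews cease. What remains is that nothing says they continue, while three places and Table 1 treat a stopped participant as being on the after-ceasing schedule. The telephone route is best effort, relies on home scales, and serves people who cannot attend an appointment; it does not create one. Nor is this merely detail left to a fuller document: the cessation anchor is stated, and it does not suit the stated analysis.

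It is also fair to say that counting the 2-year weight from discontinuation is the declared definition, and that Sample size makes 2-year analyses exploratory. The unequal timing is thus a weakness of that definition and not a contradiction.

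**Conclusion.** The point holds as a mismatch between the visit calendar and the intention-to-treat analysis. A participant who stops early and stays in the study is assured no weight at 6 months from randomisation, and reaches the 2-year visit at a different time from a completer (about week 110 against about week 130 after a stop at week 6). The timing figures rest on the cessation clock and on tablets starting at randomisation.

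The size of any bias cannot be estimated from the documents. Two stronger readings are tempting and are not supported:

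- **A share of stopping times that miss month 6.** This would assume that monthly reviews end with the tablets, and would need a visit window that the article does not give.
- **A diluted effect of 0.7 × 6.5 = 4.55 kg, set against the 6.5 kg planning effect.** This treats the projected 30% study attrition as a rate of stopping tablets while staying in the study, for which no rate is given. It also assumes that those who stop keep no effect.

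If stopping is related to tolerability and differs between arms, the missing weights would be informative. An overstated drug effect is then plausible but not demonstrated.

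**What to change.** 1. In Design overview and Outcome measures, state that every randomised participant, whether or not still taking tablets, has a clinic weight at 6 months from randomisation. This replaces the qualifier that places the 6-month weight during treatment.
2. State that monthly reviews up to that point continue for those who have stopped.
3. Keep the 1-week post-cessation review as a separate safety visit, whenever tablets stop.
4. Count the later outcome visits for everyone from the scheduled end of the 6-month treatment period, not from the individual's last tablet. This changes the definition of the exploratory 2-year outcome, so redefine it openly in Outcome measures.
5. Reconcile Indications for early withdrawal and Optimising attendance and handling missing data with Data analysis, so that it is clear whose weights are still sought after tablets stop.

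It would not be enough to let the whole follow-up series begin whenever tablets stop. That would restart every later visit at the early stop and keep the misalignment.

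**Cost.** Protocol wording, plus a few visits for early stoppers. After a stop at week 6, (26.1 − 6) / 4.345 = 4.6, so four or five monthly reviews up to and including month 6, if these were not already intended; later stops add fewer. The 1-week review and the six later visits stay the same in number. Some who have stopped will decline to attend, so some weights will still be missing.

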**Fig. 1 fig0001:**
[figure not shown]
CONSORT Diagram of study protocol. This figure outlines the flow of participants through each stage of the study, from recruitment to follow-up.

Dose adjustments will be made based on clinical indications, with input from both the clinician and the participant. Several parameters will guide these adjustments, including: 1) weight, blood pressure, and heart rate, 2) amphetamine effects, assessed using the Amphetamine Interview Rating Scale (AIRS), 3) stated adherence to the prescribed diet and exercise program.

### Participants

Potential participants will be screened to determine whether they meet inclusion criteria and any exclusion criteria prior to recruitment.

Inclusion Criteria:a)Adults aged 18–70 yearsb)BMI 25–70c)Medically stable, defined as no acute medical illness within the past 3 months, no uncontrolled chronic disease, and no recent changes in medications within past 3 months.

Exclusion Criteria:a)Significant cardiac valve disease, cardiomyopathy, or arrhythmiab)Symptomatic ischemic heart diseasec)History of addiction to illicit drugsd)Uncontrolled hypertension >140/90e)Significant kidney or liver diseasef)Uncontrolled epilepsyg)Breastfeeding, pregnant, or planning pregnancyh)Current depression or other psychiatric illnessi)Current or recent treatment (past 12 months) with psychotropic medication, systemic glucocorticoids, or weight loss medication (e.g., orlistat, phentermine)j)Family history of sudden death from cardiac causesk)Hypersensitivity to DEX or any components of the DEX or placebo tablet

All participants will be fully informed about the purpose of the study, the therapeutic and adverse effects of DEX, and will provide informed consent. Each participant will be assigned a unique study number, and data will be collected and analysed in a de-identified but re-identifiable form.

### Recruitment

Participants will primarily be recruited through general practices, using flyers and direct GP referrals. Additional recruitment methods may include digital and social media advertisements, as well as articles in community newspapers.

Potential participants will first undergo a screening interview to assess their eligibility, followed by baseline investigations for those deemed likely to qualify. Once eligibility is confirmed, informed consent will be obtained, and participants will be randomised (see Fig. 1).

GPs with an interest in obesity management, and who are able to commit to the study requirements, will be recruited as study investigators. These GPs will be trained in the study protocol and procedures, with training provided by a member of the research team.

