### Baseline investigations

a)Electrocardiography (ECG)b)Echocardiogram (ECHO)c)Blood biochemistry: Full Blood Count (FBC), Liver Function Tests (LFT), Electrolytes, Urea, and Creatinine (EUC), glucose, insulin, HbA1c, lipids, Thyroid-Stimulating Hormone (TSH), and high-sensitivity C-reactive protein (Hs-CRP)

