***Investigations***				
*Echocardiogram*	X			X
*ECG*	X		X	
*Blood test (fasted)*	X			X

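### As the Recruitment section is written, informed consent comes only after the baseline ECG, echocardiogram and fasted bloods

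*Protocol article*

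**What the plan says.** The Recruitment section of the protocol article sets the order of entry in two consecutive sentences. The first reads "Potential participants will first undergo a screening interview to assess their eligibility, followed by baseline investigations for those deemed likely to qualify". The second reads "Once eligibility is confirmed, informed consent will be obtained, and participants will be randomised".

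The Baseline investigations section defines the tests: "a)Electrocardiography (ECG)b)Echocardiogram (ECHO)c)Blood biochemistry", followed by the components of the panel. Table 1 marks the blood test as fasted. It schedules the echocardiogram and bloods at baseline and again after treatment stops, and the ECG at baseline and during maintenance.

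Three other places bear on the timing of consent or screening:

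- The Ethics row of the Specifications table says that "informed consent will be obtained from all participants prior to their inclusion in the study".
- The Participants section places screening ahead of recruitment and says that all participants will give informed consent.
- Design overview has eligible participants going through screening and baseline assessment before randomisation, and does not mention consent.

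No separate consent to screening is described anywhere.

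**The concern.** Investigations done to establish eligibility for a trial, and kept as that trial's baseline data, are trial procedures. A person should agree to them beforehand. An order that places consent after them means that people attend for an echocardiogram and give a fasted blood sample before they have agreed to take part in the research. A consent signed later cannot undo this for those who go on to be randomised, and those who drop out at this step never sign one. The article also describes no consent under which the individual test results of that second group could be used for research.

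What is at stake is participant protection and the standing of individual-level data collected before consent. The estimate of the treatment effect is not involved.

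**Working it through.** The point rests on no calculation, so the check sets the relevant sections side by side.

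**1. The stated sequence (Recruitment).** The order is: (a) screening interview; (b) baseline investigations, for those judged likely to qualify; (c) eligibility confirmed; (d) informed consent; (e) randomisation. Consent is step (d) and the investigations are step (b).

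**2. What step (b) contains (Baseline investigations; Table 1).** It contains an ECG, an echocardiogram and a fasted blood panel. The panel covers blood count, liver function, electrolytes and renal function, glucose, insulin, HbA1c, lipids, TSH and high-sensitivity C-reactive protein.

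**3. Whether these are trial procedures or usual care.** Three features point to the trial:

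- Table 1 repeats the echocardiogram and bloods after treatment stops and the ECG during maintenance. Data collection lists the ECG and echocardiogram among the baseline clinical assessments, and cardiovascular parameters are a secondary outcome. The step (b) tests are therefore the baseline half of trial measurements.
- The panel includes insulin and high-sensitivity C-reactive protein, which no listed eligibility criterion names or evidently needs. It is more than an eligibility check.
- Recruitment may also use social media and community newspapers, so some of those investigated may have no clinical reason for an echocardiogram.

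**4. Whether another section moves consent earlier.**

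| Section | What it says on timing | Does it place consent before the tests? |
|---|---|---|
| Specifications table, Ethics | Consent before inclusion in the study | No. Inclusion is not defined, and it could begin at screening or at randomisation |
| Participants | Screening comes before recruitment; all participants consent | No. It calls those being screened potential participants |
| Design overview | Eligible participants are screened and assessed, then randomised | No. Consent is not mentioned |
| Recruitment | Consent once eligibility is confirmed | No. It places consent after the tests |

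Recruitment is the only section that fixes the position of consent relative to the investigations.

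**5. Who is affected.** Everyone who reaches step (b) is tested before the consent described. If the target in Sample size is met, this includes all 58 randomised participants (29 per arm). Two further groups are tested and never consent: those found ineligible on the tests, and those who decline at step (d). The first group is foreseeable, because the exclusions include valve disease, cardiomyopathy, arrhythmia, and significant kidney or liver disease, all of which these tests would inform. The article gives no screening yield, so the size of the two groups cannot be worked out.

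**The case against.** The strongest reply is that loose wording in a condensed article is being read as a procedure. Design overview uses the word participants for people entering screening. On that usage, the Ethics row's promise of consent before inclusion could cover the screening tests. Recruitment refers to Fig. 1, which is not shown. The article also mentions a procedure manual covering recruitment, which is not shown either. A two-stage consent may well exist in the full protocol. Some of the tests might also be done in usual general practice care.

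Much of this is fair, and it limits the conclusion to the text as written. It does not remove the point. The sequence is stated explicitly, so this is not a detail that the article merely leaves out. If a screening consent exists, Recruitment misstates the order and still needs correcting. Some tests may overlap with usual care, but their repetition in Table 1 and their use as baseline data make them part of the trial.

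A reader might be tempted to infer three stronger things, which the document does not support:

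- **That everyone screened out is tested without consent.** The investigations are confined to those judged likely to qualify. Many criteria can be settled at interview, such as age, addiction history, pregnancy, recent medication and family history. People excluded there have no tests.
- **That the recruitment-rate outcome is compromised.** The plan says "Feasibility will be assessed by recruitment and retention rates" without defining the rate. A rate needs only counts of people approached, screened, eligible and randomised. A de-identified screening log can supply these, and nothing in the document bars one. Late consent restricts individual-level data, not counts.
- **That people who fail screening have no study record.** The article says that each participant receives a study number. It is silent on a screening log, and an article commonly leaves that to the full protocol.

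**Conclusion.** The point holds for the sequence as written: consent follows the ECG, echocardiogram and fasted bloods, and no other section moves it earlier or describes a consent to screening. Everyone investigated is affected, which includes all 58 randomised participants if the target is reached. Those who fail on the tests or decline afterwards never give the consent described. Any figure for that last group would rest wholly on an assumed screening yield, so none is offered.

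The conclusion assumes that Recruitment describes what will be done and that no separate screening consent sits in material not shown. If there is one, the fault is in the article's wording and not in the conduct of the trial. In either case the sample size, randomisation and primary analysis are untouched. The matter should still be settled before anyone is investigated, because a procedure carried out without consent cannot be put right afterwards.

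**What to change.** Reorder the Recruitment section to read: screening interview; written consent, either a single form or two stages with a screening consent first; baseline investigations; eligibility confirmed; randomisation. Under a two-stage scheme, the screening consent must come before any trial-specific investigation, and consent to the trial itself before randomisation.

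Then reconcile the other places with this order. State in the Ethics row what inclusion means, or replace the phrase with consent before any trial-specific procedure. Align the screening and consent statements in Participants, and add the consent step to Design overview. If the full protocol already has a screening consent, correct Recruitment to describe it.

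The cost is a wording change, with an ethics amendment if the approved procedure follows the present order, and consent discussions with some people who later fail screening. The sample size and the analysis do not change.
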